### Primary endpoint

The primary endpoint is a composite of all-cause mortality, vascular-access-related complications, permanent pacemaker implantation, stroke, re-hospitalisation due to cardiac reasons, kidney failure and major bleeding, occurring during the first 30 days after hospital discharge.

Cumulative and time-dependent (Kaplan–Meier) incidence of the primary endpoint will be compared between the 4 groups stratified according to suitability for early discharge (according to protocol) and actual discharge.

### Secondary endpoints

The incidence of the individual components of the primary outcome (between discharge and 30 days) will be evaluated for the 4 groups. Time-dependent (Kaplan–Meier) incidence of the primary outcome and its individual components will also be assessed between discharge and 12 months after TAVI.

Multivariate analysis will be performed in order to identify procedural outcomes associated with incidence of the primary endpoint in the patients that were discharged early. A further analysis will be performed to identify factors predictive of early discharge.

Other endpoints will include the length of ICU and overall hospital stay; the QoL scores at baseline, 30 days and 12 months. Other exploratory endpoints may be investigated.

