**Methods:**

The Feasibility And Safety of early discharge after Transfemoral TAVI (FAST-TAVI) registry is a prospective observational registry that will be conducted at 10 sites across Italy, the Netherlands and the UK. Patients will be included if they have been scheduled to undergo TF-TAVI with the balloon-expandable SAPIEN 3 transcatheter heart valve (THV; Edwards Lifesciences, Irvine, CA). The primary endpoint is a composite of all-cause mortality, vascular-access-related complications, permanent pacemaker implantation, stroke, re-hospitalisation due to cardiac reasons, kidney failure and major bleeding, occurring during the first 30 days after hospital discharge. Patients will be stratified according to whether they were high or low risk for early discharge (≤3 days) (following pre-specified criteria), and according to whether or not they were discharged early. Secondary endpoints will include time-to-event (Kaplan–Meier) analysis for the primary outcome and its individual components, analysis of the relative costs of early and late discharge, and changes in short- and long-term quality of life. Multivariate logistic regression will be used to identify factors that indicate that a patient may be suitable for early discharge.

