In a small prospective study (*N* = 130), early discharge was specifically targeted after elective TF-TAVI [10]. A total of 59% of patients were successfully discharged within 72 h, with one death and 3 cases of rehospitalisation occurring during the subsequent 30 days. While no death occurred in the patients that were discharged after 72 h, 7 required rehospitalisation. In a cohort of 120 patients that underwent TAVI at a single centre, 21.7% of patients were discharged on either the same day as the procedure or the following day, with a further 32.5% discharged at 2 or 3 days [6]. There were no deaths within 30 days for any of these patients, while mortality was 5.5% for those that were discharged after 4 days. Rehospitalisation rates did not differ significantly between groups.

These studies have provided preliminary data in support of the feasibility and safety of early discharge after TF-TAVI. However, if this approach is to be more widely adopted, there is a clear need for larger, prospective multicentre studies. A substantial cohort of TAVI patients would also allow for evaluation of baseline and procedural characteristics that may indicate suitability for early discharge, further decreasing the associated risks. Furthermore, the rapid advancements being made in THV and implantation technologies make up-to-date information essential.

The Feasibility And Safety of early discharge after Transfemoral-TAVI (FAST-TAVI) registry has been designed in order to provide contemporary data regarding early discharge after TAVI. This prospective, multicentre study will evaluate patients undergoing TF-TAVI with the latest generation of the balloon-expandable SAPIEN THV (SAPIEN 3; Edwards Lifesciences). In addition to assessing adverse outcomes after discharge, the dataset will enable the identification of criteria that will allow safe early discharge of patients after TF TAVI.

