### Patient stratification

Patients will be stratified when data collection for all patients is complete. A patient will be classified as being at low risk for early discharge if they fulfil all of the criteria at the point of leaving hospital, as displayed in Table 2. The patients will be further stratified according to whether they were discharged early (≤3 days post-TAVI) or late (<3 days). This will give 4 groups for comparison purposes. Further time points (e.g. stratification at hospital admission) as well as cut-offs (1, 2 or 4 days etc.) will be explored once data are available.

**Table 2 Tab2:** Patient stratification

A patient will be classified as being at low risk for early discharge if they fulfil all of the following criteria at the point of leaving hospital:
New York Heart Association (NYHA) class ≤ II
No chest pain attributable to cardiac ischaemia
No untreated major arrhythmias
Complications on day 0 to 1, but free of signs or symptoms on day 3
No fever during the last 24 h (infection-related)
Independent mobilisation and capability of self-care
Preserved diuresis (>40 ml/h during the last 24 h)
No unresolved acute kidney injury type 3 (according to VARC-2 criteria)
No red blood cell transfusion during the last 72 h
Stable haemoglobin in 2 consecutive samples (defined as a decrease of no more than 2 mg/dl)
No stroke or transient ischaemic attack (TIA)
No sign of systemic inflammation or infection (clinic or laboratory)
No haemodynamic instability

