### Statistics

As there are few reliable data on early discharge after TAVI, no formal sample size calculation was performed. Based on rates of TAVI procedures being performed, it was estimated that approximately 50 patients could be recruited in one year at each site.

Intent-to-treat analysis, defined as all patients enrolled in the registry, will be employed. Subjects will be considered registry participants when they enter the catheterisation laboratory/hybrid suite/operating room. Descriptive data summaries will be used to present and summarise the collected data. For categorical variables, frequency distributions will be given. For numeric variables, means and standard deviations or medians and interquartile ranges will be calculated, depending on data distribution. Kaplan–Meier analysis will be performed for time-to-event outcomes. Multivariate logistic regression will be performed to identify predictors of the primary endpoint in the patients discharged early, and predictors of early discharge. Variables entered into the analysis will include baseline characteristics and periprocedural complications.

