## Discussion

The FAST-TAVI registry has been designed to provide a registry of prospectively collected data that can be used to elucidate the benefits and risks of early discharge after TF-TAVI. Analysis of the results should enable identification of certain patient and procedural characteristics that indicate whether a patient requires further in-hospital monitoring or whether they could safely be discharged within just a few days after the TAVI procedure.

Preliminary data from previous studies suggest that there exists a population of patients that can be safely discharged soon after undergoing uncomplicated TAVI via the TF route [6, 8, 10, 11]. However, the human and financial costs associated with inappropriate early discharge could be immense. Complications after TAVI include bleeding, stroke and kidney injury, each associated with a mortality risk. Furthermore, all patients that undergo TAVI are at high risk for death during open cardiac surgery. They are generally elderly and display multiple comorbidities and frailty, providing an even greater risk of mortality. In addition, unplanned rehospitalisation after TAVI is expensive and so may counteract the cost savings made by discharging a patient early [14]. Studies evaluating readmission after TAVI have consistently found that heart failure is the most common cause, although the relative contributions of other factors varied [14, 15]. Furthermore, high proportions of patients were hospitalised for non-cardiovascular reasons, highlighting the complex nature of this elderly and comorbid population.

In an attempt to identify factors that indicate that an individual patient is suitable for early discharge after TAVI, Durand et al. reviewed the records of all patients that underwent TF-TAVI using the SAPIEN XT THV during a 4-year period [8]. Of the baseline and procedural characteristics that were entered into their multivariate analysis, a requirement for blood transfusion(s) and previous balloon aortic valvuloplasty were predictive of late discharge, while a pre-existing pacemaker was associated with early discharge. There was also a wide variety of univariate predictors that may have proved more influential in a larger population. The FAST-TAVI registry will build on these initial data while investigating the most recent of the SAPIEN THVs, the SAPIEN 3.

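### Kaplan–Meier to 12 months overstates the incidence of the six non-fatal components, because death is a competing event; the error is modest and limited to secondary endpoints

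*Protocol article*

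**What the plan says.** The Primary endpoint section defines a "composite of all-cause mortality, vascular-access-related complications, permanent pacemaker implantation, stroke, re-hospitalisation due to cardiac reasons, kidney failure and major bleeding", counted over the 30 days after discharge. That is death plus six components other than death.

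The Secondary endpoints section then extends follow-up: "Time-dependent (Kaplan–Meier) incidence of the primary outcome and its individual components will also be assessed between discharge and 12 months after TAVI". The abstract says the same in short form: "Secondary endpoints will include time-to-event (Kaplan–Meier) analysis for the primary outcome and its individual components". The Statistics section adds only that "Kaplan–Meier analysis will be performed for time-to-event outcomes". The article names no other time-to-event method and does not mention death as a competing event.

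On groups, Patient stratification crosses suitability for early discharge with actual discharge timing and says "This will give 4 groups for comparison purposes". The 30-day component incidences are to be evaluated for those groups. The 12-month sentence does not itself mention them.

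**The concern.** The article names both the quantity (incidence) and the estimator (Kaplan–Meier). For the non-fatal components the two do not match. A patient who dies without a stroke can no longer have one. Standard Kaplan–Meier for stroke alone censors that patient at death, which treats the patient as still able to have a stroke later. One minus Kaplan–Meier then estimates the risk in a hypothetical setting without death, and it exceeds the actual incidence whenever mortality is above zero. Because the estimator is named, this is not a detail left open for an unseen analysis plan.

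Death is not negligible here. The Discussion says of TAVI patients: "They are generally elderly and display multiple comorbidities and frailty, providing an even greater risk of mortality". A registry meant to show how often complications follow discharge should report the proportion of patients who have them. What is at stake is the level of the 12-month component incidences and, if the groups are compared on those incidences and differ in mortality, an unequal error between groups.

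**Working it through.** **Nothing to reproduce.** The article gives no 12-month mortality, component rate or power figure, and says "no formal sample size calculation was performed". The check therefore shows the size of the error over assumed ranges.

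**Inputs**
- Estimator, components and horizon: from the sections quoted above.
- 12-month mortality *m*: not given; assumed 5%, 10%, 20%.
- 12-month component risk as Kaplan–Meier would show it, *p*: not given; assumed 3%, 5%, 10%, 20%.
- Independent hazards, constant over the 12 months: assumed.

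**Formulas** (time in units of 12 months)
- Event hazard λ = −ln(1 − p); death hazard δ = −ln(1 − m).
- One minus Kaplan–Meier, deaths censored: 1 − exp(−λ) = p.
- Cumulative incidence with death as a competing event: CIF = λ/(λ + δ) × [1 − exp(−(λ + δ))].

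**One case in full.** p = 20% and m = 10% give λ = 0.2231 and δ = 0.1054. Then λ/(λ + δ) = 0.6793 and 1 − exp(−0.3285) = 0.2800, so CIF = 0.6793 × 0.2800 = 0.1902. Kaplan–Meier shows 20.0% where 19.0% of patients have the event. The excess is 0.98 points, and 0.2000/0.1902 − 1 = 5.2% in relative terms. As a check of the formula, a simulation of 400,000 patients at p = 20% and m = 20% gave 0.1803 against the analytic 0.1800.

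**Results: CIF (excess of Kaplan–Meier in points)**

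| Kaplan–Meier risk | m = 5% | m = 10% | m = 20% |
|---|---|---|---|
| 3% | 2.92% (0.08) | 2.85% (0.15) | 2.69% (0.31) |
| 5% | 4.88% (0.12) | 4.75% (0.25) | 4.49% (0.51) |
| 10% | 9.75% (0.25) | 9.50% (0.50) | 8.98% (1.02) |
| 20% | 19.5% (0.49) | 19.0% (0.98) | 18.0% (2.00) |
| Relative overstatement | about 2.5% | about 5% | about 11% |

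The relative error depends almost only on mortality. The absolute error also scales with the component's own risk.

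**Early clustering.** If half of the cumulative event hazard falls in the first 30 days (assumed), the excess at p = 20% and m = 10% drops from 0.98 to 0.56 points. If 80% falls there, it drops to 0.27.

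**At 30 days.** The Background reports an earlier single-centre cohort in which patients discharged by day 3 are compared with later discharges: "There were no deaths within 30 days for any of these patients, while mortality was 5.5% for those that were discharged after 4 days". With a 10% component risk (assumed), mortality of 0% and 5.5% gives an excess of 0 and 0.27 points.

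**Between groups.** Take two groups with the same event hazard (p = 20%) and mortality of 10% and 20%. Kaplan–Meier shows 20% in both; the actual incidences are 19.0% and 18.0%. The errors differ by 2.00 − 0.98 = 1.02 points.

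**The case against.** The case for leaving the text alone has several parts.

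*The group comparison is not in the 12-month sentence.* This stands. The four groups appear in the sentence before it, on 30-day component incidence, and in the Primary endpoint section, on the composite. A 12-month comparison of components by group is plausible but inferred.

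*Kaplan–Meier contrasts are not invalid.* This also stands. Two groups with equal event hazards and unequal mortality have equal Kaplan–Meier curves, which is correct on the cause-specific hazard scale, and a log-rank test addresses that scale. The mistake is to read the curve as the proportion of patients affected.

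*A reader might infer that the error is always largest in the group with the highest mortality, or that the groups are bound to differ in mortality.* The documents support neither. In relative terms the first holds. In absolute points it fails when component risks differ: a 2% risk with 20% mortality carries 0.21 points, and a 20% risk with 10% mortality carries 0.98. On the second, the earlier studies in the Background are mixed. One cohort had more deaths after later discharge, two retrospective series found no difference in 30-day mortality, and in the prospective study of 130 patients the only death was in the early group.

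*The bias is small against sampling error.* About 10 × 50 = 500 patients in four groups, if equal, is 125 each. The standard error of a 20% risk is √(0.2 × 0.8/125) = 3.6 points. This stands as a limit on importance. It does not make the estimator right: the bias has a known direction and does not shrink with more patients.

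*The article gives no censoring rule.* True, but censoring at death is what standard Kaplan–Meier does for a single non-fatal event, and no alternative is stated.

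**Conclusion.** Wrong as written, minor severity. For the six non-fatal components the named estimator does not give the incidence that the section sets out to report. It overstates that incidence by about 2.5%, 5% and 11% in relative terms at 12-month mortality of 5%, 10% and 20%. These sizes rest on assumed rates and on constant, independent hazards; early clustering of events makes them smaller. The direction needs only that some patients die before they have the event.

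The composite, at 30 days and at 12 months, is unaffected because death is part of it, and so is all-cause death. The 30-day component results are nearly unaffected. If the four groups are compared on 12-month component incidence and differ in mortality, the overstatement is unequal in relative terms; comparisons of cause-specific hazards remain valid.

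**What to change.** In Secondary endpoints and Statistics, and in the matching abstract sentence:

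- Keep Kaplan–Meier for the composite and for all-cause death.
- For each of the six non-fatal components, report the Aalen–Johansen cumulative incidence with death as a competing event.
- If groups are compared on these components, say which question is meant: Gray's test for differences in incidence, or cause-specific hazards for differences in event rate.

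The cost is a change of wording and of analysis code. No new data are needed, because the planned Kaplan–Meier analysis of all-cause death already requires the times of death.

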### Statistics

As there are few reliable data on early discharge after TAVI, no formal sample size calculation was performed. Based on rates of TAVI procedures being performed, it was estimated that approximately 50 patients could be recruited in one year at each site.

Intent-to-treat analysis, defined as all patients enrolled in the registry, will be employed. Subjects will be considered registry participants when they enter the catheterisation laboratory/hybrid suite/operating room. Descriptive data summaries will be used to present and summarise the collected data. For categorical variables, frequency distributions will be given. For numeric variables, means and standard deviations or medians and interquartile ranges will be calculated, depending on data distribution. Kaplan–Meier analysis will be performed for time-to-event outcomes. Multivariate logistic regression will be performed to identify predictors of the primary endpoint in the patients discharged early, and predictors of early discharge. Variables entered into the analysis will include baseline characteristics and periprocedural complications.

## Discussion

The FAST-TAVI registry has been designed to provide a registry of prospectively collected data that can be used to elucidate the benefits and risks of early discharge after TF-TAVI. Analysis of the results should enable identification of certain patient and procedural characteristics that indicate whether a patient requires further in-hospital monitoring or whether they could safely be discharged within just a few days after the TAVI procedure.

Preliminary data from previous studies suggest that there exists a population of patients that can be safely discharged soon after undergoing uncomplicated TAVI via the TF route [6, 8, 10, 11]. However, the human and financial costs associated with inappropriate early discharge could be immense. Complications after TAVI include bleeding, stroke and kidney injury, each associated with a mortality risk. Furthermore, all patients that undergo TAVI are at high risk for death during open cardiac surgery. They are generally elderly and display multiple comorbidities and frailty, providing an even greater risk of mortality. In addition, unplanned rehospitalisation after TAVI is expensive and so may counteract the cost savings made by discharging a patient early [14]. Studies evaluating readmission after TAVI have consistently found that heart failure is the most common cause, although the relative contributions of other factors varied [14, 15]. Furthermore, high proportions of patients were hospitalised for non-cardiovascular reasons, highlighting the complex nature of this elderly and comorbid population.

In an attempt to identify factors that indicate that an individual patient is suitable for early discharge after TAVI, Durand et al. reviewed the records of all patients that underwent TF-TAVI using the SAPIEN XT THV during a 4-year period [8]. Of the baseline and procedural characteristics that were entered into their multivariate analysis, a requirement for blood transfusion(s) and previous balloon aortic valvuloplasty were predictive of late discharge, while a pre-existing pacemaker was associated with early discharge. There was also a wide variety of univariate predictors that may have proved more influential in a larger population. The FAST-TAVI registry will build on these initial data while investigating the most recent of the SAPIEN THVs, the SAPIEN 3.

Often overlooked aspects of recovery after TAVI are patient comfort and the mental and emotional aspects that affect their QoL during the first few days and weeks. In a recent study looking into self-reported health and QoL changes during the first month after TAVI, Olsen et al. reported a significant improvement in the physical component summary of the SF-12 questionnaire, but not in the mental component summary [16]. The main contributing factors to the insignificant increase in the mental component were social and emotional, which is in agreement with a previous study by Krane et al. [17]. Reynolds et al. reported a significant improvement in both physical and mental scores at 6 months and one-year post-TAVI compared to baseline; however, the mental component only increased slightly during the first 30-days of follow-up [18]. It is possible that early discharge from hospital may help to improve patients’ emotional wellbeing in the first month after TAVI. In order to evaluate this hypothesis, the SF-12 questionnaire will be completed at baseline, 30 days and 12 months in the FAST-TAVI registry.

### Potential limitations

While the multinational nature of this registry increases the applicability of the findings to other countries, the differences in healthcare systems may also introduce some difficulties. This is of particular significance when evaluating the financial implications of early discharge. Furthermore, standard procedural and aftercare protocols are likely to vary between countries, and possibly between institutions within a country. However, one significant advantage of the present registry is that all patients will receive the same THV (SAPIEN 3) via the same access route (TF), reducing the variability common to the majority of prior TAVI studies.

### Potential clinical impact

The knowledge acquired from the FAST-TAVI registry should help to elucidate the relative risks and benefits of discharging a patient early after TF-TAVI. This not only includes the clinical implications for the patient, but also takes into account their QoL. Furthermore, with hospitalisation contributing significantly to the overall cost of a TAVI procedure, the potential for extending its cost-effectiveness to lower-risk patients can be explored.

## Abbreviations

CRF: Case report form
FAST-TAVI: The Feasibility and Safety of early discharge after Transfemoral TAVI
ICU: Intensive care unit
MMSE: Mini-mental state examination
QoL: Quality of life
SAVR: Surgical aortic valve replacement
SF-12: Short-form-12 quality of life questionnaire
TAVI: Transcatheter aortic valve implantation
TF: Transfemoral
THV: Transcatheter heart valve
VARC-2: Valve Academic Research Consortium-2
